#### Post-treatment surveys

Post-treatment surveys will evaluate employment status, job changes, work hours, self-efficacy to ask for accommodations, disease status, ongoing or late effects of treatment, and financial stability. Financial worry and distress will be assessed using the 12-item Comprehensive Score for financial Toxicity (COST). Participants will complete follow-up surveys 4 months after completion of all active treatment (regardless of whether the last treatment is chemotherapy, radiation therapy, or surgery). Those who have completed chemotherapy and are receiving targeted therapy only (e.g., trastuzumab with or without pertuzumab) will be considered to have completed active treatment, as will those receiving endocrine therapy. Those who undergo neoadjuvant chemotherapy and are found to have residual disease at the time of surgery may undergo additional chemotherapy with capecitabine (Xeloda) or trastuzumab emtansine (T-DM1). Patients receiving capecitabine or trastuzumab emtansine in the post-operative setting will still be considered to have completed active treatment and will be eligible for the post-treatment survey 4 months after their completion of neoadjuvant chemotherapy, surgery, and radiation therapy (if indicated). Those who have undergone surgical resection but are awaiting reconstruction will also be considered to have completed active treatment. Additional long-term follow-up surveys will be administered 1 and 2 years after completion of active treatment. For all three follow-up surveys (those administered 4 months post-treatment completion as well as those administered 1 and 2 years later), the recall period for the PRO-CTCAE® symptom questions will be 4 weeks.

#### App usage

Usage tracking analytics will be provided by Curiosity Health at Cornell Tech, including whether a user accessed the app, which sections were accessed most/least, and the duration of access.

### Plans to promote participant retention and complete follow-up {18b}

Loss to follow-up is a potential problem for any longitudinal study. Our target population includes socioeconomically disadvantaged groups who may have frequent changes of address and contact information. In the BCW study [7], which targeted a similar population, we requested contact information for a friend or family member whom we could contact if we were unable to locate the participant. We also contacted participants at intermediate time points to keep them engaged. These strategies resulted in the high retention rates described in the preceding section. We will implement a similar approach in the current study.

Participants in the RCT will be given a total of $300 in CVS gift cards over the course of the 2-year study period ($50 after each survey). Participants in the usability testing and community usability testing portion of the study will receive a total of $50 in CVS gift cards upon completion of the usability testing and the Early User Experience Survey. Participants in the focus groups and interviews will receive a total of $50 in CVS gift cards for their time. Participants will be given the option to either receive physical CVS gift card(s) or electronic CVS gift card(s) as supplies allow. CVS gift cards can be used to purchase a variety of items including food and pharmacy needs, and CVS locations are conveniently located throughout New York City and New Jersey. The study team at MSK used these cards in the BCW study [7] and received positive feedback from participants regarding their ease of use.

When necessary, interview patients may be compensated up to $150 in cash to cover cost of transportation to the interview site. Throughout our recruitment efforts, the study team has noticed that many potential participants traveling from the other NYC boroughs to Manhattan have a difficult time getting to the MSK interview site. Thus, we have increased the compensation amount to support interview participation. Prior to the interview, patients will confirm if this compensation is needed and provide the amount needed.

### Data management {19}

The data collected for this study will be managed through a REDCap (Research Electronic Data Capture) database. REDCap, a data management software system supported by Memorial Sloan Kettering Cancer Center, is a tool for the creation of customized, secure data management systems including web-based data entry forms, reporting tools, and a full array of security features including user and group-based privileges with a full audit trail of data manipulation and export procedures. REDCap is maintained on MSK-owned servers that are kept in a locked server room with appropriate environmental modifications (e.g., proper ventilation, power redundancy, and fault tolerance arrangement) and backed up nightly with some back-up tapes stored off-site. The MSK Information Systems group is responsible for applying all operating system patches and security updates to the REDCap servers. All connections to REDCap utilize encrypted (SSL-based) connections. Nationally, the REDCap software is developed, enhanced, and supported through a multi-institutional consortium led by Vanderbilt University.

Any hard copy patient-information materials will be stored in locked filing cabinets in the Department of Psychiatry and Behavioral Sciences. However, all participant surveys for this study will be completed electronically and entered by the participants and/or study staff directly into REDCap. Surveys will NOT be completed through the TEAMWork app. All data will be presented in aggregate form.

During the testing phase of the mobile app, participants will interact directly with the technology, but no information they enter will be stored or transmitted, either locally on the device or centrally on the server. During the RCT, the only data that will be transmitted from users back to the study team will be usage analytics (e.g., which components of the app are accessed, how often, and for how long). No personal information will be transmitted from the app to the study team.

### Confidentiality {27}

All data files will be password-protected and stored on secure servers in the Department of Psychiatry and Behavioral Sciences at Memorial Sloan Kettering Cancer Center. Access will be restricted to personnel working directly on this project. Files that must be shared with the rest of the study team or research coordinators will be shared using MSK’s secure file transfer system. Any printed data will be stored in locked file cabinets and will be destroyed when no longer needed. Patient identifiers will be used to link information from multiple sources. We will assign patients a random number for data analysis. The matched list of patients and random study numbers will be kept by a member of the research team in a password-protected file. No attempt will be made to identify individual patients or providers beyond the use specified in this study. Publications and presentations of the data will adhere to all requirements for the protection of patient privacy and confidentiality, and no patient or provider will be individually identifiable. All data will be presented in aggregate form.

### Plans for collection, laboratory evaluation, and storage of biological specimens for genetic or molecular analysis in this trial/future use {33}

Biological specimens will not be collected.

## Statistical methods

### Statistical methods for primary and secondary outcomes {20a}

Aim 1: To refine the TEAMWork App through usability testing in English- and Spanish-speaking women who were employed pre-diagnosis and are undergoing or plan to undergo chemotherapy for breast cancer but have low confidence in requesting workplace accommodations. Focus groups will be conducted with women who are currently employed and completed chemotherapy for breast cancer treatment.

*Analysis:* The results of usability testing will be qualitatively analyzed, with responsive iterative modifications to the app implemented concurrently in English and Spanish between waves of usability testing. Each wave will include 3-4 participants per language. Focus group results will be qualitatively analyzed. Raw data obtained from the focus groups’ audio recordings and notes will be transcribed verbatim, including silences, pauses, and exclamations by the study team and the Language Services Unit of the Immigrant Health and Cancer Disparities Service at Memorial Sloan Kettering Cancer Center, following the methodology proposed by Elderkin-Thompson & Waitzkin [60]. Translation of the transcripts from Spanish to English will be done directly from the audio recordings. Once the focus groups are transcribed, data management will be performed using NVivo Pro version 12.0, which will facilitate a systematic approach for theorizing, coding, and analyzing the data. Structural coding will be used to mark responses to questions in the interview guide [61, 62]. Codes will not be predetermined by the research team (principal investigator and co-investigators), but will emerge from the data itself. Inter-rater reliability will be assessed using percent agreement and Cohen’s kappa. A codebook will be developed as a hierarchal list of themes to guide coding for major conceptual categories and then subjected to focus coding to determine minor themes and develop analytic categories. Analytic domains will be identified from the transcripts, and major and minor thematic areas will be described and used to build a theoretical outline. Through this process, hypotheses and explanatory frameworks will be generated. A similar method will be used to transcribe, code, and analyze the notes taken during the focus groups to complement the audio transcriptions. Data from the socio-demographic assessment will be entered into a password-protected Microsoft Access database and exported. Descriptive statistics will be used to describe the study participants.

Aim 2: To evaluate the effect of the TEAMWork App on job retention after completion of adjuvant therapy for breast cancer among English- and Spanish-speaking women who were employed pre-diagnosis and plan to undergo chemotherapy.

*Analysis:* To test the TEAMWork App, we have designed a 2-arm, multicenter randomized trial that is stratified by recruitment site and language (English or Spanish). The primary analysis for which this study is powered will be a direct 2-arm comparison of job retention 4 months after treatment completion. Following this, we will fit a multivariable logistic model that includes demographic and clinical variables. Per Kahan and Morris, this model will include the two stratification variables as covariates [63]. Hypothesis testing will be done using the Wald test. We will also evaluate the relationship between job retention and confidence asking for accommodations. To account for chemotherapy-specific differences, we will evaluate the chemotherapy regimen, cycle length, and number of cycles as well as symptom burden in our analyses. To identify the most relevant symptom or symptoms for inclusion in the multivariable model, we will first conduct bivariate analyses and assess the relationship between job retention and the presence of each symptom. These analyses will include symptoms reported by at least 10% of participants. This analysis will include symptoms during the entire treatment period, such that symptoms meeting the above criteria and occurring at any time during treatment will be included. As noted, randomization will be stratified by recruitment site because it is likely there are site-specific similarities that need to be balanced when making an arm-vs-arm comparison of outcomes. However, in further analyses, we will also fit mixed effects logistic regression models where the site can be viewed as a cluster. Parameter estimates from mixed models are adjusted for site-specific correlations. To evaluate long-term endpoints, we will evaluate employment status at 1 and 2 years in similar, separate analyses.

Subaim 1: To evaluate whether the effect of the app on job retention varies by characteristics, such as chemotherapy regimen, symptom burden, race/ethnicity, language, and job type.

*Analysis:* For each of the 3 logistic regressions on job retention (one for each post-treatment time-point), we will evaluate whether there is a significant interaction with the following covariates: chemotherapy regimen, symptom burden, race/ethnicity, language, and job type. Each interaction will be evaluated separately.

Aim 3: To evaluate the effect of the TEAMWork App on confidence in asking an employer for accommodations and on receipt of accommodations during and after adjuvant therapy.

*Analysis:* The relationship between the app and confidence asking for accommodations at the mid-point of chemotherapy and 4 months post-treatment will be evaluated using chi-squared tests. In subset analyses, the relationship between job retention and receipt of accommodations will be evaluated among participants who asked for accommodations.

Aim 4: To evaluate the effect of the TEAMWork App on patient efficacy in communicating with the provider and self-reported symptom burden during and following adjuvant therapy.

*Analysis:* Participants randomized to receive the app are hypothesized to have higher efficacy in communicating with the provider and lower symptom burden during and after treatment than those randomized to the informational booklet. Perceived efficacy in patient-physician interactions as measured by the PEPPI score will be compared by arm using the 2-sample *t*-test [22]. For each symptom, we will compare symptom incidence and severity by study arm. To compare symptoms, we will conduct 2 sets of analyses. One will compare the rate of symptom incidence by assigned study arm at the mid- and end-of-chemotherapy-treatment time-points separately. A second analysis will report an arm comparison of whether patients who reported a symptom at the mid-treatment survey experienced an increase, decrease, or cessation of that symptom at the end of chemotherapy treatment. The main analytic tool that will be used for these analyses is the chi-squared test.

Exploratory aim 1: To evaluate the effect of the TEAMWork App on treatment adherence.

*Analysis:* We will compare treatment adherence (RDI) by receipt of the app in a Wilcoxon rank sum test.

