In BCW [7], approximately 50% of pre-diagnosis employed women who underwent chemotherapy were working 4 months after treatment completion. The difference in outcome between participants who did and did not have access to paid sick leave through their jobs was approximately 19% and was statistically significant (*p*=0.01). The mechanism of action of our intervention is hypothesized to be that working during the treatment period will provide job security to women and, therefore, lead to long-term job retention. Because paid sick leave provides similar job security, we will use a conservative effect size of 15% for our proposed intervention.

To identify an improvement of 15% in job retention 4 months post-treatment (i.e., 65% job-retention) in the arm randomized to receive the app, we would require 167 evaluable participants in each arm based on a 2-sided test with a 5% type I error and 80% power. We plan to recruit 420 women to obtain primary outcome data from 334 participants (assuming >80% retention 4 months post-treatment). *As noted above, we have estimated 80% retention 1 year post-treatment; we anticipate having higher retention 4 months post-treatment. Thus, we will have at least 80% power and 5% type I error to detect improvements in job-retention of 15% or more 1 year post-treatment. We expect further attrition by year 2. With a conservative 60% retention rate at 2 years, we will have 80% power to detect a difference of at least 17% for job retention at year 2. Using mixed models and important covariates, the detectable effect size for this comparison will likely decrease.*

*Sample size for sub-aim 1:* Characteristics of interest include chemotherapy regimen, symptom burden, race/ethnicity, language, and job tasks. We anticipate that, for example, 35% of participants in the study will have jobs that involve standing for long periods of time. This distribution will allow us to determine whether the association between the app and job retention varies by this job task.

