## Assignment of interventions: allocation

### Sequence generation {16a}

Study participants will be assigned to a study arm via a randomly generated list on REDCap using the Clinical Research Database (CRDB) system at Memorial Sloan Kettering Cancer Center, which allows for off-site and off-hours randomization, as needed. Randomization will be stratified by language (English and Spanish) and recruitment site. The recruitment sites for this study are MSK, Lincoln Medical and Mental Health Center, and Montefiore Medical Center.

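### Randomisation is stratified by site and language, but the primary 4-month comparison ignores both, giving up a little precision that adjustment would recover at no cost

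*Protocol article*

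**What the plan says.** Under Sequence generation {16a}: "Randomization will be stratified by language (English and Spanish) and recruitment site". With two languages and three sites this makes six strata.

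Under Statistical methods {20a}, Aim 2, the deciding analysis is fixed: "The primary analysis for which this study is powered will be a direct 2-arm comparison of job retention 4 months after treatment completion". The next sentence reads: "Following this, we will fit a multivariable logistic model that includes demographic and clinical variables". Of that second model the protocol says, citing a methods paper, that "this model will include the two stratification variables as covariates". The same paragraph explains why site was chosen for stratification: "it is likely there are site-specific similarities that need to be balanced when making an arm-vs-arm comparison of outcomes". Mixed models with site as a cluster are listed as further analyses, and the 1- and 2-year endpoints are to be handled similarly.

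Sample size {14} takes a control rate from the earlier observational study, where "approximately 50% of pre-diagnosis employed women who underwent chemotherapy were working 4 months after treatment completion", and a target of 65% in the app arm. It concludes: "we would require 167 evaluable participants in each arm based on a 2-sided test with a 5% type I error and 80% power".

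**The concern.** Balanced allocation within strata removes between-stratum variation from the true sampling variance of the arm difference. A crude two-proportion test still counts that variation as noise. If the strata are related to outcome, its standard error is therefore too large, its p-values too high and its confidence intervals too wide.

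The protocol supplies the reason to adjust. It expects site to matter for the arm comparison, and it cites a paper in support of including the stratification variables. It then applies that only to a model that is not primary.

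The later model does not repair this. Besides demographic and clinical variables, it admits symptoms from any time during treatment, chosen by bivariate association with job retention. Aim 4 hypothesises that the app lowers symptom burden, so this model conditions on something the intervention may change. It answers a different question from the primary comparison with adjustment for design factors.

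At stake is precision for the primary endpoint, in a trial sized with no cushion: 167 per arm gives 79.5% power by the pooled normal approximation.

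**Working it through.** **1. The plan's own figure.** Inputs from Sample size {14}: 50% versus 65%, two-sided 5%, 80% power. The unstratified formula with unpooled variance is

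n = [p1(1−p1) + p2(1−p2)] × (1.960 + 0.842)² / (p2−p1)² = (0.2500 + 0.2275) × 7.849 / 0.0225 = 166.6, so 167 per arm.

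This reproduces the stated figure. The sample size was therefore set for an unstratified comparison, which agrees with reading the primary analysis as unadjusted.

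**2. How the effect arises.** Let ρ be the share of outcome variance that lies between strata. With exact balance within strata, the crude standard error exceeds the true standard deviation by a factor 1/√(1−ρ). If ρ = 0, nothing is lost.

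**3. Assumptions.** The article gives neither stratum sizes nor retention by site or language, so these are assumed:
- six strata with shares 25, 15, 15, 10, 20 and 15%;
- log-odds of retention evenly spaced from worst to best stratum;
- overall rates held at 50% and 65%, with a common treatment odds ratio;
- 167 per arm, exactly balanced within strata.

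Each scenario was simulated 40,000 times. The crude test is the pooled z test; the stratified test is Cochran-Mantel-Haenszel.

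| Best-to-worst stratum odds ratio | Control rates, worst to best | Crude SE ÷ true SD (null) | Type I error, crude | Power, crude | Power, stratified |
|---|---|---|---|---|---|
| 1 | 50% throughout | 1.00 | 5.5% | 80.2% | 80.1% |
| 2 | 42% to 59% | 1.01 | 5.4% | 80.6% | 80.6% |
| 4 | 35% to 68% | 1.03 | 4.7% | 80.8% | 81.5% |
| 8 | 28% to 76% | 1.07 | 4.1% | 81.7% | 84.6% |
| 16 (extreme) | 22% to 82% | 1.11 | 3.3% | 82.6% | 87.0% |

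**4. Check on one row.** At odds ratio 8 the control rates are 28, 37, 47, 57, 67 and 76%. Their weighted variance around 50% is 0.25×0.22² + 0.15×0.13² + 0.15×0.03² + 0.10×0.07² + 0.20×0.17² + 0.15×0.26² = 0.0312. So ρ = 0.0312/0.25 = 12.5%, and 1/√0.875 = 1.07, as simulated.

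**5. Why the first row shows 5.5%.** Counts are discrete. The crude test needs a difference of about 1.96 × √(0.5/167) × 167 = 17.9 events, that is 18 or more, so the effective cut lies near 17.5. At odds ratio 1 that is (17.5/167)/0.0547 = 1.92 standard deviations, a two-sided error of 5.5%. At odds ratio 8 it is 0.1048/0.0512 = 2.05, an error of 4.1%. The drift down the column is the stratification effect; the half point above 5% at the top is not.

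**6. Other assumed layouts.**
- Two strata, odds ratio 4: power about 81.5% crude against 83.5% stratified; type I error 4.3% to 4.5%.
- Two strata, 75:25, retention 55% and 35%: 80.4% against 81.0%; type I error 4.8%.
- Two strata, 70:30, retention 53% and 43%: 80.3% against 80.4%; type I error 5.0%.

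**The case against.** The strongest reply is that a crude primary test is valid and matches its own sample-size basis. Its error is in the conservative direction, its power stays at 80% or above in every simulated scenario, and adjusted analyses are already promised. All of that stands. A reader might infer that the 5% error rate is at risk or that the trial falls short of its design; the calculations support neither.

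The loss may also be nil. At odds ratios of 1 or 2 between best and worst stratum, adjustment gains nothing. The protocol calls site similarities likely but does not quantify them. That stands too, and it is why the size is given only as a range.

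A reader might take the contrast in the Background between 57% and 93% job retention as the spread between strata and infer a large loss. The document does not support this. The contrast is by income, which is not a stratification factor, and site and language are at most partial proxies for it. Equal halves at those rates would average (57 + 93)/2 = 75%, against the roughly 50% used for sizing. The slower return to work reported for Latinas likewise concerns ethnicity rather than language, and the article attributes it at least partly to job type.

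Finally, the article does not name the primary test or use the word unadjusted. The contrast with the model that follows and the unstratified sample size still make that the natural reading. What does not stand is the suggestion that the planned adjusted model already covers the point: it is not primary, and it mixes the design factors with post-randomisation symptoms selected on outcome.

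**Conclusion.** The point holds as a modest efficiency improvement. The primary analysis leaves out the factors used to stratify randomisation, contrary to the protocol's own reasoning about site. If those factors predict job retention, the crude standard error is somewhat too large: about 1% at a best-to-worst stratum odds ratio of 2, 3% at 4 and 7% at 8. Over odds ratios of 1 to 8, the power forgone is about 0 to 3 points. An odds ratio of 16, giving about 4.5 points, is an extreme case and not an expectation.

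These sizes rest on assumed stratum shares, assumed retention differences and exact balance within strata among evaluable women. The textual finding and the direction are secure; the magnitude is not known from the document.

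**What to change.** In Statistical methods {20a}, Aim 2, define the primary 4-month test as a comparison adjusted for site and language only, both as fixed effects. Either of two forms would do:
- a Mantel-Haenszel risk difference stratified by site and language; or
- logistic regression on arm, site and language, reported as a standardised risk difference.

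With only three sites, fixed effects are preferable to a random site effect for this purpose. Report the crude two-arm comparison as supportive. Keep the model with demographic, clinical and symptom variables as a separate secondary analysis. Use the same adjusted form for the 1- and 2-year endpoints.

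The cost is about one sentence in the analysis plan, settled before outcome data are examined by arm. The sample size does not change: 167 per arm remains adequate, and any gain comes on top.

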#### The importance of working during chemotherapy in low-income survivors

In prior research, we showed that low-income breast cancer survivors who undergo chemotherapy are at higher risk of not working for 5 years after diagnosis than are women who do not undergo chemotherapy [5]. This difference in outcome is most likely due to taking time off during treatment in the absence of sick leave benefits. Nationwide, only 21% of low-wage workers have access to paid sick leave [12]. Women without sick leave who stop working have no guarantee that their jobs will be available once they are ready to return, and as a result, they are at risk of permanent job loss. The problem is exacerbated for workers in the informal sector (i.e., those who work “off the books”). Workers in this situation have no protections in case of illness under the Americans with Disabilities Act or the Family and Medical Leave Act [13–15]. In this setting, increasing their ability to work during chemotherapy could shield them from the potentially catastrophic consequences of long-term job loss. However, patients with a higher treatment-related symptom burden have lower self-reported work ability [16]. Therefore, improving symptom control during treatment is vital to optimizing patients’ ability to work.

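### The secondary adjusted job-retention models include on-treatment symptoms that the app is meant to reduce, so their app coefficient is not the total effect of assignment

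*Protocol article*

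**What the plan says.** All places are in the protocol article.

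- **Statistical methods {20a}, Aim 2.** The primary analysis, and the one the trial is powered for, is a direct two-arm comparison of job retention at 4 months. A multivariable logistic model follows, with demographic and clinical variables and the two stratification factors, tested by Wald.
- **Choice of symptoms for that model (same paragraph).** "To identify the most relevant symptom or symptoms for inclusion in the multivariable model, we will first conduct bivariate analyses". Symptoms reported by at least 10% of participants are candidates. The window is the whole treatment period: "symptoms meeting the above criteria and occurring at any time during treatment will be included".
- **Chemotherapy variables (same paragraph).** The plan will evaluate "chemotherapy regimen, cycle length, and number of cycles as well as symptom burden in our analyses".
- **Later endpoints (same paragraph).** Employment at 1 and 2 years is analysed separately in a similar way.
- **Subaim 1.** In each of the three logistic regressions, "we will evaluate whether there is a significant interaction with the following covariates: chemotherapy regimen, symptom burden, race/ethnicity, language, and job type". No time point is given for symptom burden.
- **Mechanism.** The Background says that the app is designed to optimise symptom control during treatment. The section on working during chemotherapy says that "improving symptom control during treatment is vital to optimizing" patients' ability to work. The section on self-efficacy and communication skills says that symptom burden is inversely related to work ability and job retention. Aim 4 hypothesises lower symptom burden in the app arm during and after treatment.

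**The concern.** A covariate that assignment may change should not be in a model whose arm coefficient is to be read as the effect of assignment. Here the protocol asserts both links itself: app to symptoms (Aim 4) and symptoms to work (rationale). Holding on-treatment symptoms fixed removes the part of the benefit that runs through symptom control. It also makes the arms incomparable within symptom strata if something unmeasured, such as comorbidity or job demands, drives both symptoms and working. Screening symptoms by their association with job retention favours the ones that carry most of any mediated effect.

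What is at stake is the published adjusted effect at 4 months, 1 year and 2 years. If Aim 4 succeeds, the adjusted result could look weaker than the primary result because the app worked as designed, and readers could take that as lack of robustness.

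**Working it through.** **1. The plan's own figure.** Sample size {14} says that "approximately 50% of pre-diagnosis employed women who underwent chemotherapy were working 4 months after treatment completion". It sets 65% in the app arm, with 167 evaluable per arm "based on a 2-sided test with a 5% type I error and 80% power".

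Unpooled formula: n = (1.960 + 0.842)² × (0.50×0.50 + 0.65×0.35) / 0.15² = 7.849 × 0.4775 / 0.0225 = 166.6, so 167. The stated figure reproduces; the pooled formula gives 170. The unadjusted odds ratio is (0.65/0.35)/(0.50/0.50) = 1.86. Its log is 0.619 with standard error √[1/(167×0.25) + 1/(167×0.2275)] = 0.224, so Wald power is Φ(0.619/0.224 − 1.96) = 0.79. None of this involves symptoms.

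**2. Effect of adding an on-treatment symptom.** The documents give no figure for the app's effect on symptoms or for the symptom's effect on work in this model, so the inputs below are assumptions, taken down to zero mediation.

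- Model: logit P(working) = c + θ·app + β·symptom, with β = ln 0.4.
- Symptom prevalence: m₀ = 0.60 in controls; m₁ in the app arm varied.
- Total effect held at the plan's rates. Solve (1−m₀)·expit(c) + m₀·expit(c+β) = 0.50 for c, and (1−m₁)·expit(c+θ) + m₁·expit(c+θ+β) = 0.65 for c+θ.
- The standard error of θ comes from the inverse expected information with 167 per arm. Power = Φ(θ/SE − 1.96).

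| App lowers symptom by | m₁ | θ | Adjusted app OR | SE | Wald power |
|---|---|---|---|---|---|
| 0 points | 0.60 | 0.649 | 1.91 | 0.230 | 0.81 |
| 5 points | 0.55 | 0.603 | 1.83 | 0.230 | 0.75 |
| 10 points | 0.50 | 0.556 | 1.74 | 0.230 | 0.68 |
| 15 points | 0.45 | 0.509 | 1.66 | 0.231 | 0.60 |

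In every row the true total effect is the same 15 points. The right reference is the first row, not 1.86: adjusting for a prognostic covariate that the app does not change raises the conditional odds ratio slightly and costs no power. The loss in the other rows comes from the app changing the symptom. A stronger case (60% vs 40%, symptom OR 0.3) gives OR 1.52 and power 0.43.

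**3. Risk-difference scale, with a shared unmeasured cause.** A large-sample simulation kept 50% vs 65% and assumed symptom prevalence of 50% in controls, a symptom log-odds ratio of −0.8 or −1.6, and an unmeasured cause that raises symptoms and lowers working by 0, 0.5 or 1.0 on the logit scale per SD. The standardised app effect after symptom adjustment was:

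- 15 points if the app leaves the symptom unchanged;
- 10.3 to 13.0 points if it lowers prevalence to 40%;
- 5.7 to 11.2 points if it lowers prevalence to 30%.

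The collider part shows when the shared cause is strengthened from 0 to 1.0 with the log-odds ratio at −0.8: the effect falls further, from 13.0 to 11.8 points (prevalence 40%) and from 11.2 to 8.5 points (prevalence 30%).

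**4. Interaction.** In the same simulation, with no true interaction, the fitted arm-by-symptom odds ratio stayed between 0.96 and 1.01.

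**The case against.** **The primary analysis is untouched.** This stands in full. The trial's main answer is the direct comparison, and the symptom model comes after it. A reader might infer from the power column that the trial's 80% power is at risk. It is not: those figures concern only the arm coefficient in the secondary adjusted model.

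**The adjusted model may be explanatory.** Outcomes {12} says that the four secondary outcomes, symptom burden among them, will be examined in relation to the primary outcome. That is a reasonable aim. But the Aim 2 text presents one multivariable model following the arm comparison, with the stratification factors as covariates and a Wald test, and does not label it explanatory. The arm coefficient would naturally be read as the adjusted treatment effect.

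**Number of cycles.** A reader might infer that the model also conditions on cycles actually received, changed by the app through adherence. The documents do not support this. Outcomes {12} treats the number of cycles as a feature of the regimen, the text says only that it will be evaluated, and the exploratory adherence measure is relative dose intensity, which captures dose reductions and delays. Wording that says planned cycles would be enough.

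**Subaim 1.** A reader might infer that the symptom interaction is biased. The time point is not stated, baseline PRO-CTCAE is collected, and the simulation showed no material bias. What remains is interpretive: if the on-treatment measure is used, the result cannot be read as a baseline subgroup effect.

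**The size is assumed.** This is fair. The booklet also carries advice on managing symptoms and communicating with the clinic team (Explanation for the choice of comparators {6b}), so the contrast in symptoms may be small. At 5 points the loss is modest, and at 0 there is none.

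**Conclusion.** The point holds for the secondary adjusted models at 4 months, 1 year and 2 years. That they condition on on-treatment symptoms follows from the protocol's explicit text, and that these are mediators follows from its own hypotheses. The app coefficient from these models is therefore not the total effect of assignment, and it is open to collider bias.

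The size depends on how far the app lowers symptoms and how strongly they affect work, neither of which the documents quantify. On the tabulated assumptions the adjusted odds ratio falls from 1.91 to between 1.83 and 1.66 for a 5- to 15-point reduction in symptoms, and power for that coefficient from 0.81 to between 0.75 and 0.60. With no effect on symptoms nothing is lost. The documents do not support extending the point to the powered primary comparison, to cycles received, or to a demonstrated bias in the Subaim 1 interaction.

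**What to change.** - Restrict the adjusted Aim 2 models at all three time points to variables that assignment cannot have changed: site, language, prespecified demographics, job type, planned regimen and planned cycles, and baseline PRO-CTCAE. The baseline survey is to be completed before the participant learns her arm.
- Drop the outcome-driven symptom screen from these models.
- State that symptom burden in the Subaim 1 interaction means the baseline value.
- Report on-treatment symptoms in relation to job retention in a separate analysis, labelled as mediation or explanatory, and say that its arm coefficient is not the total effect.

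This changes analysis wording only. It needs no new data, leaves the sample size and the primary analysis as they are, and keeps the examination of symptoms announced under Outcomes {12}.
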